## Abstract

**Background:**

Impulsivity and substance use disorder (SUD) are strongly interconnected, with persons scoring high on impulsivity being more vulnerable to develop substance abuse, facing more challenges for successful treatment, and being more prone to engage in criminal behavior. Studies have shown that impulsivity and craving for substances are strongly correlated. Neurofeedback is an effective treatment to reduce impulsive behavior. This study intends to determine to what extent a neurofeedback-intervention that is aimed at reducing impulsivity can also reduce levels of craving in forensic patients with SUD and comorbid Axis I and/or II diagnoses.

**Objective:**

The main objective of this study is to investigate to what extent a reduction in impulsivity by a sensorimotor rhythm (SMR)-neurofeedback intervention will lead to a reduction in craving in a population of forensic psychiatric patients with a diagnosis of SUD.

**Methods:**

Participants will be male SUD patients with various comorbidities residing in an inpatient forensic treatment facility approached through treatment supervisors for participation. Participants have tested positive for drug use in the past 24 months. The study consists of 2 parts: a randomized controlled trial (RCT) and a n-of-1 clinical series. In the RCT, 50 patients will be randomly assigned to an intervention (n=25) or a control (n=25) condition. Patients in the intervention group will receive 20 SMR neurofeedback sessions aimed at reducing impulsivity; participants in the control group receive treatment-as-usual (TAU). Additionally, 4 in depth n-of-1 clinical trials will be conducted where effects of an SMR neurofeedback intervention will be compared to effects of sham neurofeedback.

**Results:**

Results of this study are expected by the end of 2017.

**Conclusions:**

This protocol describes the design of a study testing the effects of an impulsivity-based neurofeedback protocol among forensic patients with SUD and various comorbidities. We expect a significant reduction in impulsive behavior, level of craving, and actual drug-use for participants receiving the SMR neurofeedback protocol. The n-of-1 approach might help to explain effects possibly found in the RCT study since it allows for a more direct focus on treatment effects by following participants more closely and thereby being able to directly attribute behavioral and neurophysiological change to the SMR neurofeedback protocol employed.

**ClinicalTrial:**

Dutch National Trial Register NTR5386; http://www.trialregister.nl/trialreg/admin/rctview.asp?TC=5386 (Archived by WebCite at http://www.webcitation.org/6nXLQuoLl)

## Introduction

### Background

Impulsivity has been defined as a dysfunctional trait, leading to a tendency for an individual to display behavior that is performed with little or inadequate forethought [1] and might be criminal and possibly harmful to oneself or to others [2]. Impulsivity has been operationalized in different ways with inadequate behavioral inhibition being conceived as one of the key factors [3]. Impulsive behavior is hypothesized to involve a disinhibition of cognitive control that occurs without conscious deliberation [4].

Several studies have demonstrated that substance use disorder (SUD) is strongly associated with elevated impulsivity scores on various measures [3]. In SUD, the use of a substance is continued even though a person is aware of the negative consequences of prolonged drug use. This can be explained by deficient inhibitory control over drug-taking which provides immediate (positive) reinforcement [2]. Higher levels of impulsivity were found in individuals scoring high on alcohol, stimulant, and opiate use [3] as measured by self-report instruments, such as the Barratt Impulsivity Scale (BIS-11) [4]. Individuals with combined cocaine and alcohol abuse show impaired response inhibition as compared to controls on continuous performance tasks measuring impulse control such as the cued go/no-go task [5]. Furthermore, a strong relation between elevated impulsivity scores during childhood/early adulthood and substance abuse problems later in life has been observed, indicating that heightened levels of impulsivity might precede the development of substance abuse problems (in Hawkins et al [6], for example). In alcoholism, for example, behavioral disinhibition as assessed with a novelty-seeking scale has been shown to predict early onset alcoholism [7]. Individuals scoring high on impulsivity are therefore more prone to develop SUD than healthy controls and more often exhibit antisocial behavior [7].

The concept of impulsivity has been of particular interest in studies involving criminal offenders, as these individuals often suffer from major mental disorders and are therefore more likely to be involved in criminal acts than persons without major mental disorders [8]. In criminal offenders, cluster B personality disorders and schizophrenia are frequently diagnosed [9]. Comorbidity rates between these disorders and SUD are as high as 70% [9]. Generally, treatment of SUD has proven to be difficult, with relapse rates as high as 60% after treatment in opiate abusers [10]. For patients with a criminal history and a combination of SUD and comorbid disorders characterized by high levels of impulsivity, long-term treatment outcomes are worse [9]. High impulsivity levels both predict early relapse and increase chances of premature termination of treatment [11]. This, in turn, increases the risk of recidivism in criminal behavior [12]. Adequate treatment for this vulnerable patient population is therefore extremely important, as impulsivity can be understood as an important risk factor in both the onset of SUD as well as post-treatment relapse [13].

### Neurofeedback Treatment for Impulsivity and Substance Use Disorder

Electroencephalographic (EEG) spectral analysis is a frequently used method to compare healthy controls with prolonged drug users by focusing on differences in the (relative) strength of naturally occurring rhythms in the EEG (in Alper et al [14], for example). EEG alterations most commonly found in individuals with SUD are characterized mainly by alterations in the strength of theta (4-8 Hz), alpha (8-12 Hz), and beta (12-20 Hz) frequency bands [15] and are hypothesized to be related to symptoms of drug use disorder, such as over attention to drug cues, feelings of restlessness, and loss of impulse control. Although alterations in several EEG spectral measures have been observed that vary by type of addiction, they persist even after drug abuse is in remission [14].

Neurofeedback is an intervention that uses real-time EEG measurements and displays information about these EEG measurements back to the participant, allowing them to not only see but also change their brain electrical activity over time [16]. By principles of operant conditioning, participants learn to reinforce or inhibit specific frequencies of the EEG activity [17] and thereby normalize abnormal EEG states, which in turn aims at changing abnormal psychological states [18]. Sensors are placed on the scalp and moment-to-moment information about brain activity is fed back to the participant [19].

Several studies have shown neurofeedback to be a promising intervention for various disorders, ranging from SUD to attention deficit hyperactivity disorder (ADHD) [16]. In SUD, a widely used neurofeedback protocol is the Scott-Kaiser modification of the Peniston Protocol, consisting of a combination of sensorimotor rhythm feedback (SMR, 12-15 Hz) followed by alpha-theta based feedback [17]. With this type of protocol, patients first receive neurofeedback that focuses on reinforcing SMR (12-15 Hz) while inhibiting slower frequencies such as delta (2-5 Hz) and theta (5-8 Hz) and also inhibiting high beta (ranging from 18-30 Hz) [15,17]. This type of feedback is first employed for 10 to 20 sessions before the neurofeedback protocol is switched to an alpha-theta based protocol, where alpha (ranging from 8-12 Hz) is decreased while theta (5-8 Hz) is augmented until the amplitude of alpha drops below the level of theta [15,17]. The Scott-Kaiser modification of the Peniston Protocol has shown to be effective in opiate-dependent patients as well as in patients with a mixed substance dependency, as it led to the reduction of feelings of craving [15], a powerful predictor of relapse in drug-taking [20-21] and therefore promoted treatment attendance and abstinence rates of participants [17]. As most criminal offenders with SUD also suffer from comorbid psychiatric conditions however, treatment with neurofeedback may become more complicated [16]. For patients having a combination of impulsivity issues due to comorbidity with other psychiatric disorders, as well as substance abuse problems, it is suggested that an SMR-enhancing neurofeedback protocol should be applied to address the issue of impulsivity first [22]. Studies performing a neurofeedback protocol consisting of suppressing slow waves such as theta (4-7 Hz) and enhancing faster waves such as SMR (12-15 Hz) have demonstrated an improvement of impulse control in a population of students (in Egner and Gruzelier [23], for example) and have shown to positively affect motor control and cortical inhibitory function (in Sokhadze et al [16], for example). This type of neurofeedback protocol is also commonly applied with patients suffering from the hyperactive-impulsive ADHD subtype, and there are many studies reporting reduction in impulsivity after treatment (in Fuchs et al [24], for example). Several studies have shown that impulsivity and craving for substances are strongly correlated no matter the administered drug of choice. For example, in a study by Tziortzis et al [25] with methamphetamine users, individuals with higher levels of impulsivity reported significantly more craving than individuals scoring lower on impulsivity. In alcohol-dependent patients, higher scores of craving were correlated with higher self-reported impulsivity on the BIS-11 [26]. Moeller et al [27] found a significant correlation between the motor impulsivity subscale of the BIS-11 and craving in a population of cocaine-dependent subjects. Also for cocaine-dependent patients, higher impulsivity was associated with greater severity of addiction symptoms such as craving [28,29]. Also, contemporary neuropsychological models stress impulsivity and SUD to be the result of the same imbalance between bottom-up and top-down neural systems [30,31]. Bottom-up systems concern subcortical brain circuitry promoting impulsive reward behavior (regardless of long-term outcomes), whereas top-down processes concern reflective and self-control functions driven by prefrontal brain circuitry [32]. Within SUD, chronic substance abuse may produce neural changes leading to a structural state of disinhibition and impulsivity [33,34], causing immediate reaction to substance-related cues that elicit craving [35]. Not only acute but also prolonged effects of substance abuse have proven to be of great influence in disrupting these neuropsychological mechanisms, therefore maintaining problems with inhibitory control even after drug use is terminated [36]. Although impulsivity and craving are both independently identified as key elements in SUD, to date, there has been no study investigating whether a reduction in one will also lead to a reduction of the other.

### This Study

Although the relationship between impulsivity and symptoms of SUD such as craving and actual drug use has been established, to date there is no evidence about the effects of an impulsivity-based neurofeedback protocol and its effectiveness on impulsivity and on symptoms of SUD. This study aims to examine the treatability of impulsivity with an SMR-neurofeedback intervention in a population of forensic psychiatric patients with SUD and comorbid Axis I and/or II disorders. It also aims to investigate whether a reduction of impulsivity through an SMR-based neurofeedback protocol will also result in a reduction of SUD symptoms such as craving and actual drug use.

The study will combine a randomized controlled trial (RCT) design with an n-of-1 clinical trial. The RCT allows for investigating to what extent an SMR-neurofeedback protocol can reduce craving and actual drug use by augmenting levels of impulsivity for forensic psychiatric patients at a group level. However, RCTs have several disadvantages. First, they focus on between-group differences, making it difficult to determine the exact working mechanisms of neurofeedback at the single patient level. Despite the fact that the number of studies employing neurofeedback has increased over the past 2 decades, to date the underlying working mechanisms of neurofeedback remain unclear. Success of treatment is usually determined by a reduction in subjective complaints or based on other behavioral measures, independent of patients’ responses to neurofeedback on a neurophysiological level (eg, change in mean amplitude of brain frequencies). Second, most RCTs focus on participants with single, well-defined disorders or diagnoses, making it difficult to apply previous findings to patients who have a more complex psychopathology as is usually the case in forensic patients. Third, finding a reduction in subjective complaints could partially be explained by the interaction with the person giving the treatment, as this occurs with almost all frequently given types of therapy in the psychological field [37]. To rule this out, large RCTs with a treatment and a sham arm are necessary. Unfortunately, these studies are very difficult to conduct in a forensic psychiatric setting due to the fact that forensic patients generally have low levels of treatment compliance [38]. As the current study concerns a single-site study with only a limited number of patients who fit the inclusion criteria to begin with (but on forehand sufficient according to power analysis), adding a sham arm to the RCT would most likely further reduce the motivation of patients to participate and hence increase nonresponse. However, insight into possible sham effects is needed to differentiate between specific and nonspecific treatment effects which are independent of the neurofeedback trainer. Finally, RCT studies showing treatment effects of neurofeedback often vary in the applied protocols, number of sessions, and treatment intensity. To date, there have been no guidelines developed that specify these neurofeedback parameters. Especially for forensic patients, developing a treatment that is well applicable and helps to reduce symptoms of SUD is of great importance, as forensic treatment is aimed at protecting society and reducing the risk of reoffending. By adding several n-of-1 clinical trials we attempt to cope with these disadvantages. A well-conducted n-of-1 trial allows testing of the specific working mechanisms of neurofeedback in a single patient and is therefore able to detect detailed behavioral and neurophysiological changes that can then be attributed more definitely to neurofeedback treatment.

### Objectives

Primary outcome variables are the degree of impulsivity as measured with the Dutch version of the BIS-11 [39]; inhibitory control as measured with a cued go/no-go reaction time task [40]; degree of drug craving as measured with an altered version of the Desire for Alcohol Questionnaire (DAQ) [41]; actual drug use as measured with urine, saliva, or breathalyzer analysis; and changes in resting state EEG pattern.

Primary objective: To what extent does a reduction in impulsivity by using SMR-neurofeedback result in a reduction of core symptoms of SUD such as craving and actual drug use in a population of forensic psychiatric patients with a diagnosis of SUD?

Secondary objectives:

1. To what extent can an SMR-based neurofeedback intervention reduce levels of impulsivity as measured by BIS-11 and a cued go/no-go task in a population of forensic psychiatric patients with a diagnosis of SUD?

2. To what extent can an SMR-based neurofeedback intervention reduce levels of craving as measured by self-report questionnaire DAQ-SF (short form) in a population of forensic psychiatric patients with a diagnosis of SUD?

3. To what extent can an SMR-based neurofeedback intervention reduce actual drug use as measured with urine, saliva, or breathalyzer analysis in a population of forensic psychiatric patients diagnosed with SUD?

## Methods

### Overview

This study will be conducted according to the principles of the Declaration of Helsinki (version 59, Seoul, October 2008) and in accordance with the Medical Research Involving Human Subjects Act. It has been approved by the medical ethical council of Brabant, the Netherlands (study number NL46390.008.13).

This study takes place in Forensic Psychiatric Centre (FPC) Dr S van Mesdag, a maximum security inpatient forensic treatment facility in Groningen, the Netherlands. Patients in this treatment facility are male criminal offenders with at least one Axis I or II diagnosis and considered to be at risk for criminal recidivism if not treated properly. About 70% of all patients treated in this facility have a comorbid diagnosis of SUD [9].

### Randomized Controlled Trial

A randomized controlled trial with N=50, where 25 participants are randomly assigned to treatment as usual (TAU) combined with 20 SMR-based neurofeedback sessions and 25 participants are randomly assigned to TAU only, without neurofeedback intervention. The 2 groups are compared pretreatment (T0) and posttreatment (T1) on variables linked to the research questions. Both groups will receive pre- and posttreatment measurements with an interval between T0 and T1 of approximately 10 weeks in which participants in the intervention group will receive 20 neurofeedback treatment sessions and participants in the control condition will follow TAU.

The design of this part of the study is a 2×2 design with the condition (neurofeedback vs TAU) as a between-subjects factor and time as a within-subjects factor (pre- and postintervention).

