### Participants

A power analysis calculation for the RCT using G*Power 3 (Department of Psychology) based on a 1-tailed alpha value of .05, a power value of 0.80, and an effect size (*f*) of 0.80 yielded a recommended sample size of 21 participants each in the control and intervention conditions. Given the special research population we aim to select 25 participants for each condition.

Participants are male patients diagnosed with SUD (substance dependency or substance abuse) according to the *Diagnostic and Statistical Manual of Mental Disorders*, Fourth Edition, Text Review (DSM-IV-TR [43]) and currently staying at the treatment facility. Participants have tested positive for drug use in the past 24 months at time of inclusion. Drug use is operationalized as urine, saliva, or breathalyzer analysis testing positive for either marijuana and/or psychostimulant/opioid drugs and/or alcohol. Corresponding with treatment facility policy, nonprescribed medication that is used for recreational drug consumption such as inhaled methylphenidate will also be scored as positive drug testing, as will refusal to undergo drug testing.

Participants are allowed to continue using prescription medication (as prescribed by a psychiatrist or general physician of the treatment facility) but are required to inform researchers of any medication they are currently using or any change in medication during treatment with neurofeedback.

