#### Randomized Controlled Trial

Resting state EEG data will be analyzed using custom-made Matlab R2012b scripts [51]. A repeated measures multivariate analysis of variance with factors condition (neurofeedback vs control) and frequency band (delta, theta, alpha, beta, or gamma) will be conducted. If main or interaction effects are observed, post hoc tests will be used to determine which levels of the factors are explaining the observed effects.

Repeated measurement with time (pre- [T0] and postintervention [T1]) as the within-subject factor and group (control vs intervention) as the between-subject factor will be conducted for the DAQ-SF, BIS-11, IFTE, and IFTE-SR. If main or interaction effects are observed, post hoc test will be used to determine which levels of the factors are explaining the observed effects. A repeated measures analysis of covariance will be conducted to examine differences in actual drug use as dependent variables to test for a moderating effect of impulsivity on craving and actual drug use.

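### The T0/T1 repeated-measures analysis planned for DAQ-SF and BIS-11 amounts to an unadjusted change-score test on complete pairs; a baseline-conditioned model is more precise and resists baseline-related loss of T1

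*Protocol article*

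**What the plan says.** In the Methods, under Randomized Controlled Trial, the timing of T1 is common to the arms: "Both groups will receive pre- and posttreatment measurements with an interval between T0 and T1 of approximately 10 weeks". The same sentence describes what fills that interval, giving an "interval between T0 and T1 of approximately 10 weeks in which participants in the intervention group will receive 20 neurofeedback treatment sessions", while control men continue with TAU. That section calls the design a 2×2, with condition between subjects and time within subjects.

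Under Statistical Analysis, Randomized Controlled Trial, DAQ-SF, BIS-11, IFTE and IFTE-SR are to be analysed by "Repeated measurement with time (pre- [T0] and postintervention [T1]) as the within-subject factor" and group as the between-subject factor. Neither section adjusts these outcomes for their baseline value.

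Three other statements bear on how complete T1 will be:
- This Study: "forensic patients generally have low levels of treatment compliance".
- Background: "High impulsivity levels both predict early relapse and increase chances of premature termination of treatment". BIS-11 impulsivity is listed as a primary outcome under Objectives.
- Participants: the calculation returns 21 per arm, and then "Given the special research population we aim to select 25 participants for each condition". No dropout rate is given.

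**The concern.** A two-time-point, time-by-group repeated-measures analysis has two properties that matter here. It uses only men with both T0 and T1. Its interaction test is also the square of the two-sample t test on change, so baseline enters with a fixed coefficient of 1 and not the coefficient that the data support.

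The first property matters if men are lost in a way related to their baseline. Completers in the depleted arm then start from a different mean, and regression to the mean appears as a group difference. The second matters in every case: at realistic correlations the change score discards precision, and this trial has only 25 men per arm.

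The extra men recruited above 21 per arm protect power. They do not protect comparability.

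**Working it through.** **The plan's own figure.** A two-sample t test with a standardised mean difference of 0.80, one-sided alpha 0.05 and power 0.80 needs 21 per arm (exact power 0.817). This matches the stated number when 0.80 is read as a standardised difference in means. At 25 per arm the power is 0.874. The margin is 25 − 21 = 4 men, or 16%.

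**Inputs.** From the article: 25 men per arm and two time points. Assumed, because the article gives no value: T0-T1 correlation ρ of 0.5 to 0.7, unit SD at both times, no true effect, and 4 men lost, all from the neurofeedback arm (the plan's own margin).

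**Precision with no loss.**
- SE of the change contrast: √[2(1 − ρ) × 2/25].
- SE of the baseline-conditioned contrast: √[(1 − ρ²) × 2/25].
- Ratio: √[2/(1 + ρ)].

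| ρ | SE, change | SE, conditioned | Ratio |
|---|---|---|---|
| 0.5 | 0.283 | 0.245 | 1.155 |
| 0.6 | 0.253 | 0.226 | 1.118 |
| 0.7 | 0.219 | 0.202 | 1.085 |

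Estimating the slope with 50 men inflates the conditioned SE by about √(47/46) = 1.01. The ratios then become about 1.14, 1.11 and 1.07. A simulation with 25 per arm gave the same values. The change contrast therefore has an SE about 7 to 15% larger. Ignoring the small slope correction, 25 men per arm analysed by change carry the information of 25 × (1 + ρ)/2 = 18.75 to 21.25 men per arm analysed with baseline conditioning.

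**Bias when loss depends on baseline.** Under no effect, expected change given baseline y is −(1 − ρ)y. If the completers' baseline mean is m SD below that of the full arm, the change contrast is biased by (1 − ρ)m. Higher scores are worse on both scales, so this counts against neurofeedback.
- Fairly strong but not absolute selection of high scorers gives m of about 0.22. The four lost men then average 0.22 × 21/4 = 1.16 SD above the mean.
- At ρ = 0.5: 0.5 × 0.22 = 0.11 SD. At ρ = 0.7: 0.3 × 0.22 = 0.07 SD.
- The SE with 21 v 25 men is √[2(1 − ρ)(1/21 + 1/25)] = 0.296 and 0.229, so the bias is about 0.3 to 0.4 SE. Two-sided type I error rises only to about 6 to 7%.
- Weaker and stronger selection spans about 0.05 to 0.14 SD. The bias is zero if loss is unrelated to baseline.
- Conditioning on baseline brings the bias to 0.00 in simulation.

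**Bias when loss depends on response.** If the four men lost are instead poor responders, the change contrast is biased by 0.18 to 0.25 SD in favour of neurofeedback, with two-sided type I error of 14 to 15%. A baseline-conditioned model still gives about 12 to 13%. Measuring T1 in all 50 men restores about 5%.

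**The case against.** A reader might infer from "interval between T0 and T1 of approximately 10 weeks in which participants in the intervention group will receive 20 neurofeedback treatment sessions" that T1 is reached only after 20 sessions, so that men who stop neurofeedback go unmeasured in that arm alone. The article does not say this. The full sentence begins with both groups and sets a common interval of about 10 weeks. The 20 sessions are what is planned within it, not a condition for T1. No section excludes men who stop or restricts the analysis to completers. Under Recruitment, the financial reward is tied to completing the measurements, not the sessions, and applies to everyone. Drug tests and the clinician-scored IFTE are routine facility data. Control men can miss T1 too, and similar loss in both arms would largely cancel the bias. How early stoppers and missing T1 are handled is detail that an article may leave to the full protocol. All of this stands.

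It can also be said that the compliance remark explains why a sham arm was avoided, that the increase to 25 is not described as a dropout allowance, and that every bias figure rests on assumed loss. This is fair too. The bias range is conditional, and its low end is small.

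A third argument is that the article does not name the SPSS procedure, so a mixed model may be intended. That is possible but strained: the design is described as a 2×2 between/within layout, and the neighbouring analyses are a repeated-measures multivariate analysis of variance and an analysis of covariance. Even an unconstrained mixed model would return the change contrast when data are complete, so the loss of precision would remain.

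**Conclusion.** The point holds as a criticism of the analysis that is stated, and not as a claim that the trial will leave men who stop unmeasured. For DAQ-SF and BIS-11, the planned test is an unadjusted change-score comparison on complete pairs.

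The loss of precision, about 7 to 15% in the SE, depends only on a T0-T1 correlation of 0.5 to 0.7. It applies even if every man is measured. The bias of about 0.07 to 0.11 SD needs more: loss that depends on baseline, 4 of 25 men, in the neurofeedback arm only. The article makes some loss plausible but quantifies none of it.

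This is a worthwhile improvement to the plan, not an error that invalidates the trial.

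**What to change.** Under Statistical Analysis, Randomized Controlled Trial, replace the repeated-measures analysis of DAQ-SF and BIS-11 with a baseline-conditioned model, analysing all randomised men as allocated. Either of these would serve:
- a mixed model for T0 and T1 with a common baseline mean and the group contrast at T1, which keeps men who lack T1; or
- analysis of covariance on T1 adjusted for T0, which uses men with T1 and is also unbiased when loss depends only on baseline and the adjustment is linear.

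In the Methods, under Randomized Controlled Trial, add a sentence confirming that T1 is taken at about 10 weeks in both arms whatever number of sessions was attended. This is needed because the model change does not cure response-driven loss.

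The cost is wording. SPSS 19 can fit both models, and no further patients or measurements are needed beyond the T1 already planned. The one drawback is that some men may be assessed before session 20, which would slightly dilute the effect of the full course.
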